# Influence of early goal-directed therapy using arterial waveform analysis on major complications after high-risk abdominal surgery: study protocol for a multicenter randomized controlled superiority trial

**DOI:** 10.1186/1745-6215-15-360

**Published:** 2014-09-16

**Keywords:** High-risk surgery, Early goal-directed therapy, Hemodynamic monitoring, Hemodynamic optimization, Tissue oxygen delivery, Randomized controlled trial, Outcome, Quality of life, Cost-effectiveness

## Abstract

**Background:**

Early goal-directed therapy refers to the use of predefined hemodynamic goals to optimize tissue oxygen delivery in critically ill patients. Its application in high-risk abdominal surgery is, however, hindered by safety concerns and practical limitations of perioperative hemodynamic monitoring. Arterial waveform analysis provides an easy, minimally invasive alternative to conventional monitoring techniques, and could be valuable in early goal-directed strategies. We therefore investigate the effects of early goal-directed therapy using arterial waveform analysis on complications, quality of life and healthcare costs after high-risk abdominal surgery.

**Methods/Design:**

In this multicenter, randomized, controlled superiority trial, 542 patients scheduled for elective, high-risk abdominal surgery will be included. Patients are allocated to standard care (control group) or early goal-directed therapy (intervention group) using a randomization procedure stratified by center and type of surgery. In the control group, standard perioperative hemodynamic monitoring is applied. In the intervention group, early goal-directed therapy is added to standard care, based on continuous monitoring of cardiac output with arterial waveform analysis. A treatment algorithm is used as guidance for fluid and inotropic therapy to maintain cardiac output above a preset, age-dependent target value. The primary outcome measure is a combined endpoint of major complications in the first 30 days after the operation, including mortality. Secondary endpoints are length of stay in the hospital, length of stay in the intensive care or post-anesthesia care unit, the number of minor complications, quality of life, cost-effectiveness and one-year mortality and morbidity.

**Discussion:**

Before the start of the study, hemodynamic optimization by early goal-directed therapy with arterial waveform analysis had only been investigated in small, single-center studies, including minor complications as primary endpoint. Moreover, these studies did not include quality of life, healthcare costs, and long-term outcome in their analysis. As a result, the definitive role of arterial waveform analysis in the perioperative hemodynamic assessment and care for high-risk surgical patients is unknown, which gave rise to the present trial. Patient inclusion started in May 2012 and is expected to end in 2016.

**Trial registration:**

This trial was registered in the Dutch Trial Register (registration number NTR3380) on 3 April 2012.

**Electronic supplementary material:**

The online version of this article (doi:10.1186/1745-6215-15-360) contains supplementary material, which is available to authorized users.

## Background

### High-risk surgery

Both the extent of the surgical procedure and the presence of comorbidities increase the risk of an adverse outcome after surgery. Moreover, approximately 12.5% of all surgical patients are considered as ‘high-risk’ [1, 2]. The majority of perioperative complications and death occur in this minority of patients [1]. With increasing age and comorbidities in the general population, the number of high-risk surgical patients is expected to grow. Approximately 50% of these surgical patients develops one or more perioperative complications, and mortality in this specific patient group is around 5% [1–6]. Major complications such as myocardial infarction, cardiac failure, stroke, pneumonia, renal failure, or sepsis, involve a significant burden to the patient and to hospital facilities during the hospitalization period [3]. After discharge, these complications may result in long-term disability, cognitive impairment and even death, significantly reducing quality of life and increasing healthcare consumption [3].

### Hemodynamic monitoring in high-risk surgery

Surgical patients are subject to the effects of anesthesia, direct surgical trauma, inflammation, fluid shifts, and blood loss. In extensive surgical procedures these effects are enhanced, which may impair oxygen delivery to organs and tissues. Patients with significant comorbidities have limited cardiopulmonary reserve and are therefore more susceptible to the consequences of surgical stress [7]. An imbalance in tissue oxygen delivery and demand may occur, which promotes the incidence of complications [8–10]. This emphasizes the need for appropriate hemodynamic monitoring and optimization therapy to maintain adequate tissue oxygen delivery in perioperative care for this high-risk group.

Cardiac output (CO) is the principal determinant of tissue oxygen delivery. Continuous monitoring of CO would therefore be valuable for each high-risk surgical patient. A number of CO measurement techniques are available. Pulmonary artery thermodilution remained the standard technique for a number of decades [11, 12]. This technique is, however, invasive and associated with potentially life-threatening complications which limits its use in clinical practice [11, 12]. Transesophageal echocardiography (TEE) can be used to measure CO, but is also rather invasive, does not provide CO continuously, and requires specific skills that are not included in the training of each anesthesiologist or intensive care physician [13]. Therefore, TEE is predominantly used in cardiac surgery. Esophageal Doppler probes for continuous CO measurement are easier to use but not readily tolerated by conscious patients. Other minimally invasive CO techniques such as bioimpedance are not yet sufficiently reliable for use in clinical practice [13].

Arterial waveform analysis (AWA) provides a less invasive and more practical alternative to conventional techniques of CO monitoring. CO is derived from the arterial pressure waveform and only requires an arterial line, which is almost routinely placed in high-risk surgical patients in the operating room (OR) and intensive care unit (ICU) [13, 14]. Moreover, the AWA technique enables dynamic preload assessment in mechanically ventilated patients. Assessment of cardiac preload or fluid responsiveness is the first step in optimizing CO [14, 15]. Both AWA-based CO measurement and dynamic preload assessment have been validated in a variety of clinical settings [14, 16]. The technique is therefore potentially valuable for advanced hemodynamic monitoring and fluid optimization of high-risk, non-cardiac surgical patients [17].

### Early goal-directed therapy

Adequate strategies to correct and improve hemodynamic variables should be available, since monitoring without therapeutic consequences is not enough. Early goal-directed therapy (EGDT) refers to the preemptive use of predefined target values for hemodynamic optimization in order to maintain tissue oxygen delivery. A target variable is continuously monitored and immediately corrected using a treatment algorithm if the value decreases below a predefined threshold. Especially CO or CO-derived variables have been used for this purpose. The treatment algorithms used in EGDT guide fluid therapy and inotropic support, in order to improve the patient’s hemodynamic status. With the emergence of AWA techniques, a new, promising CO measurement technique became available for EGDT [14, 18].

### Previous literature

Before the start of the study we performed a systematic review of the literature to evaluate all available evidence on the use of EGDT in elective, high-risk, abdominal surgery (Additional file 1). The results indicated that EGDT is a promising strategy to reduce morbidity and even mortality in high-risk surgery. There are, however, several limitations to the previous literature which may explain why EGDT has never been widely implemented into routine practice [19]. First, the results from most studies are outdated and not applicable to the current standard of care. In studies from 1988 to 2000, morbidity and mortality are much higher in comparison with current practice, even in the intervention groups. The same applies for length of stay in the hospital. Second, pulmonary artery catheterization has been used for the purposes of EGDT at that time. As described before, this technique is limited to specific types of surgery and not broadly accepted for perioperative monitoring in non-cardiac surgery [11–13, 20]. Two studies applying arterial waveform analysis for EGDT purposes were small and performed in a single center [4, 6]. Moreover, minor complications, such as short-lasting intraoperative hypotension or urinary tract infection, are included as an outcome measure. These complications are not associated with increased long-term morbidity and mortality and should be evaluated separately. One final but major limitation applies to all of the studies described. They lack information about the effect of EGDT on long-term outcome, quality of life, and utilization of healthcare resources. This hinders a cost-effectiveness analysis. EGDT requires the purchase of CO monitoring equipment which consists of specific patient monitors and arterial blood pressure sensors. Additional costs may be the result of an increased use of inotropic support or other therapeutic consequences of EGDT.

Since the start of the trial in May 2012, a number of interesting studies have been published which partially addressed the shortcomings mentioned above [5, 21–23]. Two studies demonstrated that the implementation of a goal-directed strategy was cost-effective [21, 22]. In addition, two multicenter studies were performed in which a reduction in complications was shown [5, 23]. However, minor complications were included, and the number of patients was rather small in these studies.

### Added value of the proposed study

The present study is a multicenter, randomized controlled trial in a relatively large group of patients and performed in both university and non-academic teaching hospitals. Patients scheduled for elective high-risk abdominal surgery are included. They represent an extensive group of patients at risk for adverse postoperative outcomes. The primary aim is to reduce the number of major complications that are associated with an increased short-term and long-term morbidity and mortality. These complications are expected to comprise a major burden to quality of life, healthcare costs, and long-term outcome, which are included as secondary outcome parameters. AWA-based CO monitoring techniques are used to assess tissue oxygen delivery, which are minimally invasive and easy-to-use. The treatment algorithm is straightforward and suitable for each anesthesiologist, ICU physician, and anesthesia or ICU nurse. The results of this study may therefore be useful in guiding evidence-based implementation of EGDT.

### Objective

The primary objective of the study is to investigate the effect of perioperative EGDT using arterial waveform analysis on a composite endpoint of major complications, including mortality after high-ris, abdominal surgery, in comparison with standard care. Secondary endpoints are minor complications, length of stay in the hospital, length of stay in the ICU or post-anesthesia care unit (PACU), long-term outcome, quality of life (QOL), and cost-effectiveness. We hypothesize that perioperative EGDT using AWA reduces the number of major complications after high-risk abdominal surgery in comparison with standard care.

## Methods/Design

### Trial design

The EGDT trial is designed as a multicenter, randomized, controlled superiority trial with two parallel groups in a 1:1 allocation. The trial is unblinded for the clinicians involved, the patients, and the observers.

### Study setting

Currently, the study is performed in three hospitals in The Netherlands: Albert Schweitzer Hospital (Dordrecht, The Netherlands), University Medical Center Groningen (Groningen, The Netherlands), and University Medical Center Utrecht (Utrecht, The Netherlands). The Maastricht University Medical Center (Maastricht, The Netherlands) is preparing study participation. Additional participating centers may be added in the future.

### Eligibility criteria

Eligible are patients scheduled for elective high-risk abdominal surgery. Two groups of patients are considered high-risk: patients undergoing extensive procedures comprising a high risk for an adverse postoperative outcome, irrespective of the condition of the patient (group 1); patients undergoing moderately extensive procedures that suffer from significant comorbidity (group 2). These procedures comprise a moderately high-risk for an adverse postoperative outcome in healthy patients, but are considered high-risk for patients with significant comorbidity.

Inclusion criteria are:Group 1: patients scheduled for the following operations in which postoperative observation in the ICU/PACU is needed, irrespective of their American Society of Anesthesiologists (ASA, Table 1) physical status: esophagectomy, pancreaticoduodenectomy, open abdominal aorta aneurysm repair, and major abdominal resections for soft tissue malignancy.Group 2: patients with ASA physical status III or IV scheduled for the following surgical procedures in which postoperative observation in the ICU/PACU is needed: gastrectomy, colorectal resections for carcinoma, and other extensive upper or lower abdominal surgery (such as ileocystoplasty or debulking surgery for ovarian cancer).

**Table 1 Tab1:** **American Society of Anesthesiologists (ASA) physical status**

ASA physical status	Description
I	Normal, healthy patient
II	Patient with mild systemic disease which does not affect daily functioning (such as controlled hypertension, stable chronic obstructive pulmonary disease (COPD), well-regulated diabetes mellitus, mild obesity)
III	Severe systemic disease which affects daily functioning (such as coronary artery disease, heart failure or COPD limiting exercise tolerance, morbid obesity)
IV	Systemic disease that is a constant threat to life (such as invalidating COPD or heart failure, unstable angina pectoris)
V	Moribund patient

Patients will be excluded if they meet one of the following criteria: patients with aortic insufficiency > grade 1, patients who are under 18 years-old, patients with cardiac arrhythmias (such as atrial fibrillation or flutter, or ventricular tachycardia), patients requiring emergency surgery, patients in which cardiac output measurement is mandatory for therapeutic decisions, or contraindication for passive leg raising in the entire postoperative period.

### Randomization

A randomization procedure is used to allocate patients to standard care (control group) or standard care with EGDT (intervention) in a 1:1 ratio. The randomization is stratified according to hospital and type of surgery. In each stratum, a block randomization with variable block size is applied using a computer.

### Standard care

Patients assigned to standard care will be treated according to local routine, with the following conditions: 1) after induction of anesthesia and tracheal intubation, patients are mechanically ventilated (volume control) with a fixed tidal volume of 8 ml/kg^-1^ (ideal body weight, IBW) throughout the procedure, adjusting respiratory rate to maintain normocapnia; 2) an arterial line, central venous line, and urine catheter are placed, 3) hypotension after induction is treated preferably with crystalloids, eventually with colloids, with a maximum of 500 ml. Ongoing hypotension is treated with a continuous infusion of norepinephrine. Sudden, short-lasting hypotension is treated with phenylephrine or ephedrine depending on local routine and indication; and 4) transfusions with erythrocytes will be applied according to the 4-5-6 rule (Additional file 2).

Therapy is aimed at maintaining: S_p_O_2_ ≥ 95%, mean arterial blood pressure (MAP) ≥ 60 mmHg or ≤ 25% below baseline in cases of preexisting hypertension, and heart rate (HR) < 100/min or ≤ 25% above baseline.

The use of epidural analgesia, enhanced recovery after surgery (ERAS) protocols, corrections for preoperative fasting, and basic fluid regimes is allowed but not obligatory. Serum lactate, central venous oxygenation saturation, and other laboratory parameters may be used to the discretion of the attending anesthesiologist or ICU physician.

### Intervention

Patients assigned to EGDT are treated according to the same conditions as defined for the standard group. An EGDT algorithm is added to standard care in order to maintain tissue oxygen delivery in the perioperative period. After induction of anesthesia in the OR, an AWA technique is applied for continuous CO measurement and dynamic preload assessment. The choice of AWA technique depends on the institution in which the study is performed. CO values are indexed to the patients’ body surface area. For each patient, an age-dependent target cardiac index (CI) is determined with the following criteria: age < 60 years, target CI ≥ 2.8 l/min/m; age between 60 and 75 years, target CI ≥ 2.6 l/min/m; or age > 75 years, target CI ≥ 2.4 l/min/m.

If the CI drops below the target value, a treatment algorithm is used in order to restore the CI above the threshold (Figure 1). In this algorithm, the dynamic preload parameter stroke volume variation (SVV) is used to determine whether the patient should receive a fluid challenge (FC), or whether inotropic support should be started or increased. Continuous infusion of norepinephrine and/or dobutamine should be used as inotropic support. SVV cannot be used in the following circumstances: spontaneous breathing activity, tidal volume <8 ml/kg, and/or breathing frequency >16/min^-^.

**Figure 1 Fig1:**
[figure not shown]
**EGDT algorithm.**
^(1)^target value depends on age: age < 60 years: target CI ≥ 2.8 l/min/m^2^; age between 60 and 75 years: target CI ≥ 2.6 l/min/m^2^; or age > 75 years: target CI ≥ 2.4 l/min/m^2^. ^(2)^”no” in the presence of spontaneous breathing activity, tidal volume < 8 ml/kg, or breathing frequency > 16/min. ^(3)^CI increases: repeat FC. If not: increase inotropic support. CI = Cardiac Index, FC = Fluid Challenge, PLR = Passive Leg Raising, SVV = Stroke Volume Variation, Tidal volumes are in ml/kg ideal body weight (IBW); IBW is calculated as 22 × L^2^ (L = length in meters).

In these circumstances, a passive leg raising (PLR) test is used to guide fluid or inotropic support [24–26]. The procedure is explained in Figure 2. If the CI increases 10% or more during PLR, a 500 ml FC is given. If not, inotropic support is started or increased. If both measurement of SVV and PLR testing are not possible, a small 250 ml FC is given. If the CI subsequently increases, another 250 ml FC is given. If the CI does not increase, inotropic support is started or increased. Treatment according to this EGDT algorithm starts after induction of anesthesia in the OR and is maintained until discharge from the ICU/PACU, with a maximum of 24 hours from induction of anesthesia.

**Figure 2 Fig2:**
[figure not shown]
**Passive leg raising (PLR) test.** The patient is transferred to the PLR position, in which the legs are lifted at an angle of 45° for 120 seconds. This should be performed by pivoting the entire bed.

### Modifications

In case of any newly developed arrhythmia in patients in the intervention group, CO and SVV measurements obtained with AWA are unreliable. Therefore, treatment according to the EGDT algorithm stops as long as the arrhythmia persists. If a patient in the intervention group develops unwanted tachycardia, arrhythmia, or (suspected) myocardial ischemia due to inotropic support applied within the EGDT algorithm, inotropic support needs to be reduced or stopped, irrespective of the CI. In addition, a FC should be withheld or stopped if pulmonary edema or cardiac decompensation is suspected, irrespective of the CI.

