### Risk assessments

The treatment algorithm introduced in the patients assigned to EGDT includes measurement of cardiac output, SVV, and PLR as a test. These measurements are performed using the arterial catheter, which is routinely placed in patients undergoing high-risk, non-cardiac surgery. Therefore, no additional catheters are placed in comparison with routine hemodynamic monitoring. EGDT involves fluid therapy and inotropic support, which are commonly used in patients undergoing high-risk surgery. Additional risk associated with its use in the treatment algorithm is therefore not likely in comparison with routine practice. The systematic review of the literature performed before this study (Additional file 1) reported adverse events due to the use of pulmonary artery catheters, which are not used in this study. Only one study reported myocardial ischemia due to use of inotropic support, which disappeared after stopping inotropic infusion [6]. In the other studies however, the results point to a lower incidence of myocardial ischemia, although significant reductions have not been reported. Adverse events with respect to fluid overload have not been described in the systematic review. Despite this, precautions have been taken in the EGDT algorithm to prevent the potentially harmful effects of excessive fluid and inotropic support.

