#### Safety

Our systematic review of the literature did not reveal any harm due to the use of fluid or inotropes in goal-directed strategies. In the OR and ICU/PACU, both fluid and inotropes are extensively used. We decided to allow the use of both crystalloid and colloid fluids, according to local preferences. Norepinephrine and dobutamine were chosen for inotropic support as these inotropes are commonly used. Clinicians and other healthcare personnel are therefore familiar with the administration, clinical effects, and adverse reactions. In the algorithm however, patients may end up in a continuing loop of fluid or inotropic support if the response in CI is insufficient. In this case, volume overloading or adverse effects of inotropes may occur, and a number of safety measures have been incorporated in the algorithm in order to address this. If tachycardia, arrhythmia, myocardial ischemia, pulmonary edema, or cardiac decompensation is suspected or observed, any intervention within the algorithm should be stopped immediately. In contrast, fluid or inotropes should not be withheld in patients with CI values above their target. We therefore emphasize that EGDT is added to standard care and does not replace it. Interventions within the usual care for high-risk surgical patients, such as treatment of hypotension, hypovolemia, or any other suspicion of hemodynamic deterioration, should therefore be applied irrespective of the CI or the treatment algorithm.

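### For unwanted tachycardia and suspected myocardial ischemia, the Methods make restraint of inotropes depend on the cause of the event, while the Safety section does not

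*Protocol article*

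**What the plan says.** In the Methods, the Modifications section covers unwanted tachycardia, arrhythmia and (suspected) myocardial ischemia in the intervention group in one sentence. It applies when the event is "due to inotropic support applied within the EGDT algorithm, inotropic support needs to be reduced or stopped, irrespective of the CI". The same section suspends the whole algorithm for any newly developed arrhythmia and withholds fluid challenges when pulmonary edema or decompensation is suspected. Neither of those two rules asks about cause.

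In the Discussion, under Clinical considerations, the Safety section lists tachycardia, arrhythmia, myocardial ischemia, pulmonary edema and cardiac decompensation. It says that if one of these "is suspected or observed, any intervention within the algorithm should be stopped immediately".

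The default that these rules restrain is in the Intervention section. When CI is below target and passive leg raising does not raise it by at least 10%, the instruction is: "If not, inotropic support is started or increased". On the drugs, the section says: "Continuous infusion of norepinephrine and/or dobutamine should be used as inotropic support". It also says: "Patients assigned to EGDT are treated according to the same conditions as defined for the standard group". Those conditions, under Standard care, include this one: "Ongoing hypotension is treated with a continuous infusion of norepinephrine".

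The Risk assessments section relies on the brake. It says that "precautions have been taken in the EGDT algorithm to prevent the potentially harmful effects of excessive fluid and inotropic support", and reports from the literature review: "Only one study reported myocardial ischemia due to use of inotropic support, which disappeared after stopping inotropic infusion".

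**The concern.** The two sections set different triggers for the same two events. A clinician or nurse working from the Methods must first decide that algorithm inotropes caused the tachycardia or ischemia. One working from the Safety section need only suspect the event.

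What is at stake is the safety of the individual patient. If suspected ischemia has another or unclear cause and CI is below target, the Methods text shown still points towards starting or raising dobutamine or norepinephrine. Other causes are foreseeable in this population. Group 2 patients must be ASA III or IV, Table 1 gives coronary artery disease and unstable angina as examples of those classes, and neither is an exclusion criterion.

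**Working it through.** No statistical figure in the protocol bears on this point, so the check is a comparison of texts.

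**The two rules for tachycardia and ischemia**

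| | Modifications (Methods) | Safety (Discussion) |
|---|---|---|
| Trigger | Event caused by algorithm inotropes | Event suspected or seen, cause not mentioned |
| What is restrained | Inotropes | Any algorithm intervention |
| Action | Reduce or stop | Stop at once |

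**Applying both rules to a patient whose CI is below target and who does not respond to fluid**

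1. *Event caused by algorithm inotropes.* Both texts act. They differ in action and scope only.
2. *On algorithm inotropes, event from another cause (for example blood loss or pre-existing coronary disease).* The Modifications sentence does not apply, so the Intervention default stands. The Safety section stops the algorithm.
3. *Not yet on algorithm inotropes.* The cause condition cannot be met. The Modifications sentence does not bar a first start of inotropes; the Safety section does.
4. *Norepinephrine running for hypotension and for CI.* It is a standard-care drug and also one of the two algorithm inotropes. The document does not say how an event is then attributed, so it is unclear whether the Modifications sentence applies. The Safety section stops the algorithm.
5. *New arrhythmia.* The Methods suspend the whole algorithm whatever the cause, so there is no gap.

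The gap is therefore in cases 2 to 4, for tachycardia that is not a new arrhythmia and for ischemia. That is 2 of the 5 events in the Safety section, and the inotrope branch only.

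**Ceiling on exposure to the rule**

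Inputs: 542 planned patients with 1:1 allocation, and about 160 recruited by the end of 2013 (Trial status).

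- Still to recruit: 542 − 160 = 382, and 382/542 = 70.5%.
- Intervention arm: 382/2 = 191.

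The 191 are future patients who would be treated under the rule. The document gives no basis for estimating how many would meet cases 2 to 4.

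**The case against.** The strongest reply is that the Safety text is Discussion prose summarizing the Modifications section. Its stop sentence follows remarks about volume overload and adverse effects of inotropes arising from the algorithm, so a causal setting may be implied. The two rules can also be obeyed together, since stopping under the Safety section never breaches the Modifications section. Figure 1 is not shown and may carry a further precaution. Standard care aims at a heart rate below 100/min or at most 25% above baseline, so the Methods are not silent on tachycardia. Trial experts can be consulted at any time, and a cause condition is clinically defensible because tachycardia is non-specific and can accompany low output.

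Much of this stands, and it limits the point to the written rule. It does not remove it. The heart rate aim is a treatment goal, not a stop rule, and says nothing about ischemia. If the causal phrase is read as attached to ischemia alone, ischemia still carries the condition. If the Safety text is only a loose summary, its trigger is still wider than the rule it summarizes.

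A reader might infer two stronger claims, and the document supports neither:

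- *That the Methods forbid stopping unless the algorithm caused the event.* The sentence says what to do in that case and prohibits nothing in others.
- *That norepinephrine makes cause impossible to judge.* Dual use can make it ambiguous. The problem does not arise for dobutamine, which is named only as an algorithm drug, or for norepinephrine started only for CI. How often the two uses overlap is not stated.

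**Conclusion.** The point holds as a modest inconsistency in a patient-safety rule. For unwanted tachycardia and suspected ischemia, the Methods make restraint of inotropes conditional on cause and the Safety section does not. Where the cause is different or unclear, or algorithm inotropes have not been started, the Methods text shown leaves the start-or-raise default unrestrained. The norepinephrine overlap adds to the difficulty, but the mismatch in triggers stands without it.

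This rests on the printed text and on the assumption that Figure 1 contains no separate brake for these events. The 191 patients are a ceiling on exposure to the rule. The number affected is unknown. It would go beyond the document to infer that patients were harmed or that the trial's results are affected, and neither is claimed.

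**What to change.** Remove the cause condition in the Modifications section for these two events. Suggested wording:

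> When unwanted tachycardia or myocardial ischemia is suspected or observed in an intervention-group patient, whatever the presumed cause, no inotrope is started or increased to reach the CI target, and any being given for that target is reduced or stopped regardless of the CI. Norepinephrine is then titrated only to the standard-care blood pressure aim.

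The last sentence avoids having to divide one infusion into two purposes: from that moment only the blood pressure aim governs it.

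Use the same action, reduce or stop, in the Modifications and Safety sections. Do not narrow the range of interventions that the Safety section stops, since it is the more protective text. Leave the arrhythmia suspension and the fluid-challenge rule as they are.

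The cost is an IRB amendment and a briefing of staff in the three recruiting centers, and in the fourth before it starts. There is also a small clinical price: in some patients whose tachycardia has another cause, the CI target will not be pursued with inotropes. Treatment of hypotension and other deterioration under usual care is unaffected, because the Safety section already requires it independently of the algorithm. Sample size, data collection and analysis do not change.
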